## 3.5 WITHDRAWAL OF A TRIAL PARTICIPANT:

- If the patient worsens, and mucormycosis expands beyond the range of inclusion criteria
- If the patient is in need of the ventilator support
- If the participant is unwilling to continue or turns non-compliant

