| **Inclusion Criteria** | - Stage 1 and 2 (Staging document annexed) of ROCM - Age > 18 years - All genders - Fungal smear analysis through KOH staining/ microscopy of affected area showing presence of mucormycetes (to save precious time), followed by following exploratory imaging techniques:   - CEMRI (for ruling out Stages 3 and 4)   - CT-guided endoscopy-cum-biopsy (for detailed histopathology study) |
| **Exclusion Criteria** | - ROCM cases in stages 3 and 4(Staging document annexed) presenting with bony erosion, cerebral vascular invasion, invasion into the cranium, orbital apex or cribriform plate of the ethmoid bone, cavernous sinus (II-VI cranial nerve palsies) will be excluded. - Diagnosed cases of Pulmonary ,Cutaneous, Gastrointestinal ,Advanced, disseminated mucormycosis will be excluded. - Pregnant and lactating women. - In the opinion of the clinical team, progression to death is imminent and inevitable within the next 24 hours, irrespective of the provision of treatments. |
| **Follow-up period** | - Patient will be assessed clinically twice a day; MRI/endoscopy-cum-biopsy will be assessed on day 1, 14 and 28. |
| **Outcomes** | **Primary Outcome**   1. Change in condition as seen in standard imaging or other diagnostic techniques:  - MRI contrast in ROCM cases   **Secondary Outcomes**   1. To assess difference in the survival of the patients in both the groups during hospitalization. |
| **Endpoint** | - Recovery as per the outcome parameters, followed by discharge from hospital - Advanced, disseminated mucormycosis - Death of the patient |
| **Study Product, Dose, Route** | - Individualized homoeopathic medicine in appropriate dose, orally, four times daily; or more frequently in severe cases. |
| Placebo | Placebo group patients will receive identical placebo (globules moistened with dispensing alcohol) as an add on to standard protocol treatment. Dose repetition will be a in similar pattern to medicine group. |
| Duration of administration | Maximum 28 days (depending on the patient’s admission duration) |
| Statistical Methodology | All primary efficacy analyses will be conducted in the Intention-to-treat (ITT) population; thus, all randomized patients should be included in the primary analysis. |
| Funding Agency | Central Council for Research in Homoeopathy, Ministry of AYUSH, Govt. of India |
| Budget | Rs. 75 lakhs approx. |

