## 3.3 ELIGIBILITY CRITERIA

### INCLUSION CRITERIA:

- Confirmed cases* of covid-related ROCM .
- Age > 18 years
- All genders
- ***Confirmation of each type of mucormycosis will be based upon** respective inclusion criteria:

| **S.No** | **Type of Mucormycosis** | **Inclusion criteria** |
| --- | --- | --- |
|  | **ROCM** | - Stage 1 and stage 2 (Staging document annexed) of ROCM will only be included). - Fungal smear analysis of the affected site reporting presence of mucormycetes (to save precious time), followed by MRI and/or biopsy - *MRI contrast imaging**   *MRI will show Mucosal thickening with T2 hypointense components at T2W images, Nonenhancement of involved mucosa/soft tissue at Post contrast T1W images, Marrow edema and enhancement of adjacent bones and skull base at Fat- saturated T2W and postcontrast T1W image. ^[[66]](#endnote-66)^ . Hyperintense lesion extending from paranasal sinus along orbital apex into intracranial structures and narrowing or slow flow in the ipsilateral internal carotid artery in the vicinity of mucor invasion seen in T2W^[[67]](#endnote-67)^.   - KOH staining/ microscopy and Biopsy**** of affected area   ****Biopsy will show non-septate/pauci-septate, ribbon-like hyphae (at least 6–16μm wide), Vessel occlusion)^[[68]](#endnote-68)^. |

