**Statistical analysis:**

Data collected will be compiled on to a MS Office excel worksheet & will be subjected to statistical analysis using an appropriate package like SPSS software. Descriptive statistics like frequency (n) & percentage (%) of categorical data, mean & Standard deviation of numerical data in each group / subgroup will be depicted.

Frequency (n) & percentage (%) of various categories in each group / subgroup will be compared using chi square test.

Normality of numerical data will be checked using Shapiro – Wilk test or Kolmogorov-Smirnov test. Depending on the normality of data, statistical tests will be determined.

For a numerical continuous data following a normal distribution, inter group comparison (2 groups) will be done using t test, else a non parametric substitute like Mann Whitney U test will be used.

Intra group comparisons for a numerical continuous data following a normal distribution will be done using paired t test (for 2 observations) or repeated measures ANOVA for >2 observations, else a non parametric substitute like Wilcoxon signed rank test (for 2 observations) or Friedman’s test for >2 observations will be used.

Frequency (n) & percentage (%) of various responses in each time interval will be compared using chi square test / McNemar’s test.

Keeping alpha error at 5% and Beta error at 20%, power at 80%, p<0.05 will be considered statistically significant.

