## STATISTICAL METHODS

Data analysis will be done through Intention To Treat (ITT) method, thus, all randomized patients should be included in the primary analysis. Additional analyses (e.g. subgroup analysis as per age, sex, perceived risk categories will also be carried out. Statistical advice will be sought before initiation. Kolmogorov-Smirnov tests will be used to analyse the normality of the data distribution. Data will be presented in number, percentage, Mean with 95% Confidence Interval, SD, Median, IQR. Statistical significance will be considered as the p value<0.05. Correlations between individual diagnoses/symptoms/ characteristics will be calculated in a Spearman rank correlation table. Correlations between groups of symptoms will be explored by principal component analysis (PCA). Comparison of baseline characteristics and outcome among all participants will be done by using parametric or non-parametric test. For categorical data χ2 exact test will be used. Concordance of the different methods for appraising result will be measured by Cohen’s kappa and Spearman rank correlation.

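### Section 3.5 withdraws patients for outcome-related reasons and provides for no outcome data afterwards, which conflicts with the all-randomised primary analysis

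*Protocol*

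**What the plan says.** Section 3.5 of the protocol, on withdrawal of participants, gives three triggers:

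- progression: "If the patient worsens, and mucormycosis expands beyond the range of inclusion criteria";
- ventilation: "If the patient is in need of the ventilator support";
- unwillingness or non-compliance: "If the participant is unwilling to continue or turns non-compliant".

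The range in the first trigger comes from the inclusion criteria in section 3.3: "Stage 1 and stage 2 (Staging document annexed) of ROCM will only be included". The trigger is therefore met once disease passes Stage 2 of the annexed staging.

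The Endpoint row of the synopsis lists recovery with discharge, followed by "Advanced, disseminated mucormycosis - Death of the patient". Section 3.6 makes change on contrast MRI the primary outcome and survival during the hospital stay the secondary one. On the analysis population, the synopsis says "All primary efficacy analyses will be conducted in the Intention-to-treat (ITT) population", and the Statistical Methods section says "all randomized patients should be included in the primary analysis".

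Three other places bear on the point. Section 3.4 (Details of intervention) deals separately with medicines that are stopped, and asks for the reason to be recorded. Section 3.4 (Duration of intervention) arranges telephone contact on days 14 and 28 for patients discharged early. The Laboratory Investigations table schedules sinus MRI at D0, D14 and D28, or at other times as management requires. None of the three mentions a withdrawn patient.

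**The concern.** What section 3.5 withdraws is the participant, not the study product. Because stopped medicines are handled elsewhere, a site would naturally read 3.5 as the patient leaving the trial. No section then tells the site to go on collecting MRI or survival status.

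The first trigger is the disease getting worse, which is what the primary outcome measures. It also overlaps the listed endpoint of advanced disease. All three triggers may come before death. If the patients who do badly leave the data, and do so at different rates in the two arms, those who remain are no longer a randomised comparison. The survival comparison may also lose patients at high risk of dying. Non-compliance is not defined and the trial is single blind, so that judgement may be made by someone who knows the arm.

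**Working it through.** **The plan's own figures.** The protocol gives no rate of progression, ventilation or withdrawal, so there is no stated figure for this point to reproduce. The yardstick is the target difference of 0.10 under Target Sample Size. The formula there reproduces: (1.96 + 0.84)² × 0.09 / 0.10² = 70.56, rounded to 71. How 71 per group relates to 72 in total is a separate matter. At 36 per arm, as in the synopsis, a difference of 0.10 is 0.10 × 36 = 3.6 patients. The advice to recruit 5–25% more for attrition is not added to the 72.

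**Assumptions.** Let r be the share of an arm that recovers and w the share withdrawn for progression, with everyone withdrawn counting as not recovered. All values of r and w below are assumed.

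**Formulas.** With all randomised patients kept and withdrawals counted as failures, the difference is r(adjuvant) − r(control). With withdrawn patients lost, each arm shows r / (1 − w).

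| Case (adjuvant / control) | All randomised | Non-withdrawn only | Difference |
|---|---|---|---|
| r 70/60%, w 15/25% | +10.0 | 0.70/0.85 = 82.4% v 0.60/0.75 = 80.0% | +2.4 |
| r 70/60%, w 20/30% | +10.0 | 0.70/0.80 = 87.5% v 0.60/0.70 = 85.7% | +1.8 |
| r 70/60%, w 20/20% | +10.0 | 0.70/0.80 = 87.5% v 0.60/0.80 = 75.0% | +12.5 |
| r 60/60%, w 25/15% | 0 | 0.60/0.75 = 80.0% v 0.60/0.85 = 70.6% | +9.4 |
| r 60/60%, w 30/20% | 0 | 0.60/0.70 = 85.7% v 0.60/0.80 = 75.0% | +10.7 |
| r 60/60%, w 30/30% | 0 | 85.7% v 85.7% | 0 |

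Swapping the arms in the fourth and fifth rows gives −9.4 and −10.7. With no true effect, the spurious benefit goes to the arm that progressed more.

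**Patients left.** Of 36 per arm, 32.4, 28.8, 25.2 and 21.6 remain at 10%, 20%, 30% and 40% withdrawn.

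If withdrawn patients are followed or counted as failures, the all-randomised column is kept in every row.

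**The case against.** The strongest reply is that section 3.5 is silent on data after withdrawal, and silence is not exclusion. The protocol twice requires all randomised patients in the primary analysis. It keeps every patient on conventional management and allows MRI at other times as needed. Its survival outcome is in-hospital, so hospital records could supply it. The event that causes a withdrawal is itself known, and a chi-square comparison can count that patient as a failure. Missing-data handling may sit in an SAP that is not shown.

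Much of this stands, and it rules out several stronger readings that a reader might infer:

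- **That an intention-to-treat analysis cannot be done, or that withdrawn patients have no later MRI or survival status.** The text says neither. The analysis is possible if these patients are followed or counted as failures; the protocol does not secure it.
- **That ventilation is a listed endpoint.** It is not. Spread beyond Stage 2 also only overlaps advanced, disseminated disease: the exclusion criteria list the two separately, and Stage 3a is limited orbital involvement with vision unaffected.
- **That the named tests, such as "repeated measures ANOVA for >2 observations", drop withdrawn patients from the arm comparison.** The Statistical analysis section assigns them to comparisons within a group, so they do not bear on this point.
- **That the comparison is biased in a known direction.** The equal-withdrawal rows show a widened effect in one case and no shift in the other.

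The reply does not remove the core. An SAP can say how missing values are handled, but it cannot recover data that the protocol never told sites to collect. The withdrawal rule is fixed in the protocol, and its triggers depend on outcome.

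**Conclusion.** The point holds in this form: the protocol withdraws participants for outcome-related reasons and for non-compliance, does not separate stopping study product from ending follow-up, and provides for no outcome data afterwards. That conflicts with its all-randomised requirement.

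If withdrawn patients leave the data, the comparison is at risk of bias whose size and direction the documents do not fix. In the cases shown, the distortion is of the same order as the 0.10 the trial is designed to detect. These cases are illustrations, not bounds. They rest on assumed rates and on a yes/no recovery outcome, whereas section 3.6 says only change on MRI. The point should be fixed before recruitment, because outcome data not collected may not be recoverable later.

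**What to change.** - In section 3.5, state that progression beyond Stage 2, ventilation and non-compliance do not end follow-up. Separate non-compliance from unwillingness to continue, and reserve loss of follow-up for withdrawal of consent.
- Unless consent is withdrawn, record for every randomised patient the survival status in hospital, as the secondary outcome is defined, and at Day 28 if obtainable, together with any MRI done in routine care. The present telephone contact covers only patients discharged early, so it needs extending.
- In the all-randomised primary analysis, count death and progression beyond Stage 2 as unfavourable outcomes.
- Reconcile the synopsis (Endpoint and Statistical Methodology rows), Duration of intervention, sections 3.5 and 3.6, the Laboratory Investigations table and Statistical Methods.

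Whether and when study product stops is left to the clinical team. The cost is protocol wording and a short status check per withdrawn patient; no additional MRI is asked for.

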## 3.6 OUTCOMES

#### Primary:

Change in condition as seen in standard imaging or other diagnostic techniques:

- MRI contrast in ROCM cases

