#### Secondary:

- To assess difference in the survival of the patients in both the groups during hospitalization.

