## LABORATORY INVESTIGATIONS

| **INVESTIGATIONS** | | |
| --- | --- | --- |
| - **Lab parameters** | CBC, ESR, FBS, PPBS, HbA1C, LFT, KFT with electrolytes | D0 and as per IMP |
| - **Imaging technique** | - CEMRI of Brain with orbits and sinuses. | - (Only at inclusion) |
|  | - CEMRI PNS | - D0 (or latest report if it is within 03 days of enrolment day), D14 and D28, or before or after as per IMP/ requirement |
|  | - CT guided endoscopy-cum-biopsy Fungal smear/KOH staining | - As per IMP, if required |

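### The primary outcome, change on contrast MRI, gives death no value, although the protocol promises that all randomised patients enter the primary analysis

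*Protocol*

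**What the plan says.** Section 3.6 of the protocol defines the primary outcome as "Change in condition as seen in standard imaging or other diagnostic techniques" and names one technique, "MRI contrast in ROCM cases". The synopsis says the same. The Laboratory Investigations table times the sinus MRI at "D0 (or latest report if it is within 03 days of enrolment day), D14 and D28, or before or after as per IMP/ requirement".

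Death is placed elsewhere. The only secondary outcome is "To assess difference in the survival of the patients in both the groups during hospitalization". The synopsis Endpoint row lists "Death of the patient" beside recovery and advanced disease, but neither section 3.6 nor the statistical sections refer to that row.

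On the analysis set, the Statistical Methods section says "thus, all randomized patients should be included in the primary analysis", and the synopsis repeats it. The Statistical analysis section gives chi-square for categories and, for normally distributed numerical data, "inter group comparison (2 groups) will be done using t test, else a non parametric substitute like Mann Whitney U test will be used". No section states how a death is scored in the primary outcome.

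**The concern.** The protocol foresees deaths. They are a listed endpoint and the subject of the only secondary outcome, and the only prognosis-based exclusion is death expected within 24 hours. A patient who dies before a follow-up scan cannot have an MRI change, so the outcome definition and the all-randomised promise cannot both be met for that patient.

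Two errors become possible. If one arm loses more of its sickest patients, the scanned survivors in that arm look better, and the comparison is no longer the randomised one. Conversely, a benefit that works by keeping patients alive would not appear in the primary result.

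**Working it through.** **Inputs from the protocol.** 36 patients per arm (synopsis), a design difference in proportions of 0.10 and a variance term of 0.09 (Target Sample Size). The sizing figure reproduces: (1.96 + 0.84)² × 0.09 / 0.10² = 70.56. It serves here only to fix 10 points as the yardstick.

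**Inputs assumed.** The protocol gives no mortality rate and no improvement rate by arm, so all rates below are assumptions.

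**1. Can the listed tests include every randomised patient?**
- *Numeric change (t test or Mann-Whitney).* Each patient needs a value. A patient who dies before any follow-up scan has none. These tests then run on scanned survivors.
- *Proportion improved (chi-square).* Everyone can be in the denominator, but only under a rule that death counts as not improved. No such rule is stated.
- *Death between D14 and D28.* Such a patient may have a D14 scan. The protocol does not say which scan is primary.

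**2. False benefit among survivors.** Let m be the share of all randomised patients who are alive and improved, equal in both arms, and d the mortality. With death as not improved, the true difference is m − m = 0. Among survivors, the improved share is m/(1 − d). With m = 0.70, 10 points of excess death in one arm, all among non-improvers, and every death unscanned:

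| Control mortality | Arm with more deaths | Control | False benefit |
|---|---|---|---|
| 5% | 0.70/0.85 = 82.4% | 0.70/0.95 = 73.7% | 8.7 points |
| 10% | 0.70/0.80 = 87.5% | 0.70/0.90 = 77.8% | 9.7 points |
| 20% | 0.70/0.70 = 100% | 0.70/0.80 = 87.5% | 12.5 points |

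The last row is the limit of the assumption: every survivor in the arm with more deaths has improved.

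**3. A less extreme mix.** Per arm, take 24 good-prognosis patients (80% improve) and 12 poor-prognosis patients (20% improve if alive), with deaths only in the poor group and no treatment effect on MRI.
- 2 v 6 deaths: survivors 21.2/34 = 62.4% v 20.4/30 = 68.0%, +5.6 points for the arm with more deaths. All randomised with death as not improved: 21.2/36 = 58.9% v 20.4/36 = 56.7%, −2.2 points.
- 3 v 9 deaths: survivors 21.0/33 = 63.6% v 19.8/27 = 73.3%, +9.7 points. All randomised: 58.3% v 55.0%, −3.3 points.
- 4 v 4 deaths: 20.8/32 = 65.0% in both arms, difference 0 either way.

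**4. Numeric change.** In a simulation (5,000 trials per setting, 36 per arm, no treatment effect on MRI change, death correlated 0.7 with poor change), the t test among survivors favoured a given arm significantly in 2.7% of trials when both arms had 10% deaths. It favoured the arm with more deaths in 6.4% at 20% v 10% and in 13.9% at 30% v 10%. The nominal rate in one direction is 2.5%.

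**5. Benefit through survival only.** With 10% v 20% dead and survivors improving at rate r in both arms, the all-randomised difference is r × (0.90 − 0.80), which is 8 points at r = 0.8 and 10 points at r = 1.0. The difference among survivors is 0.

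**The case against.** The strongest reply is that the protocol nowhere says deaths are dropped; it says the opposite. A reader might infer that the plan prescribes a survivors-only comparison. The text does not support that. The trial is sized on proportions and chi-square is available, so deaths could be counted as not improved, and the Endpoint row offers categories that need no scan from the dead. That stands as a possible reading, but the row is never tied to the outcome or the tests, and the scoring rule is unwritten.

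A reader might also infer that anyone who dies before D28 lacks a follow-up scan. That is too strong: a D14 scan may exist, and the imaging schedule allows scans at other times. Only deaths before any follow-up scan leave no MRI change at all.

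The size is open to challenge too. Only stages 1 and 2 enter, so mortality may be low. Every biased example needs unequal deaths concentrated in patients with poor scans. With equal deaths the shift is nil or immaterial, so this is no evidence of a built-in tilt towards either arm.

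Finally, handling of missing outcomes is often left to a statistical analysis plan, which is not shown. How death counts is different. It is part of what the primary outcome is, the protocol fixes that outcome, and no missing-scan rule can recover a scan that could never be made.

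**Conclusion.** The point holds in this form: the primary outcome leaves death without a value while the protocol requires all randomised patients in the primary analysis. For a numeric change the two cannot be reconciled as written; for a proportion they can, given one added rule. The protocol should be changed.

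The possible distortion is about 9 to 12.5 points with 70% of randomised patients improved in both arms, 10 points of excess death in one arm, control mortality of 5% to 20%, and all extra deaths among non-improvers and unscanned. The mixed-prognosis example gives about 6 to 10 points. Both are comparable to the 10-point design difference. These are illustrations on assumed rates, not predictions, and the distortion vanishes or is immaterial when deaths are equal.

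**What to change.** Amend section 3.6 and both statistical sections to state that death from any cause by study D28 is scored as failure if the primary outcome is a proportion, or as the worst rank if it is a numeric or ordinal MRI change, compared by Mann-Whitney. Show deaths by arm and MRI change among survivors separately, as supportive results.

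State that vital status is confirmed at study D28 for every randomised patient. This is not assured now: the survival outcome covers only the hospital stay, and section 3.4 times the post-discharge telephone contacts by day of illness. Aligning the existing day-28 call to the enrolment day would supply it.

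Living patients without a scan, such as those withdrawn under section 3.5 or followed only by telephone after discharge, need their own rule. Scoring deaths does not cover them.

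The cost is a short amendment and confirmation of D28 vital status after discharge, with no extra patients or scans. The small downside is that the primary result becomes a composite of death and MRI change, which is why both components must be shown.

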## TARGET SAMPLE SIZE:

Sample size was determined using the expected proportion of event / outcome in each group values of which are estimated from literature & using the formula,

n= (Z_α_ + Z_β_)^2^ [p q]

(p-q) ^2^

where Z_α_ is the z variate of alpha error i.e. a constant with value 1.96

Z_β_ i.e. a constant with value 0.84

p, q are proportions of the variable, values of which are taken from the parent article.

Approximate estimates:

1. 80% power
2. Type I error to be 5%
3. Type II error to be 20%
4. Difference in proportions between the groups to be 0.10

Substituting the values,

n= (1.96+ 0.84)^2^ [0.09)]

(0.10)^2^

n= 70.56

A minimum of **71 subjects per group** completing the study would be giving a good external validity. Since the number has to be equally divided in both the groups, **72 participants will be enrolled.**

For follow-up studies, to avoid loss by loss to follow up / attrition, kindly consider recruiting 5-25% more subjects so that even after attrition, we would be able to achieve the required minimum sample size.

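### The primary outcome is an unscaled change on contrast MRI with no event, threshold or deciding day, although the trial was sized on a proportion with an event that is never named.

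*Protocol*

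**What the plan says.** **Outcome.** Protocol section 3.6 and the Outcomes row of the synopsis define the primary outcome as "Change in condition as seen in standard imaging or other diagnostic techniques". The only item listed beneath it is "MRI contrast in ROCM cases". No MRI measure, grade, direction or responder threshold follows. The synopsis row on endpoints offers "Recovery as per the outcome parameters, followed by discharge from hospital", which points back to outcome parameters that carry no threshold.

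**Timing.** The follow-up row of the synopsis states "MRI/endoscopy-cum-biopsy will be assessed on day 1, 14 and 28". The Laboratory Investigations table schedules contrast MRI of the paranasal sinuses at "D0 (or latest report if it is within 03 days of enrolment day), D14 and D28, or before or after as per IMP/ requirement". Neither document location names D14 or D28 as the deciding assessment.

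**Sizing.** The Target Sample Size section opens with "Sample size was determined using the expected proportion of event / outcome in each group" and uses a difference of 0.10. It does not say which event it means.

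**Test.** The Statistical analysis section says "Depending on the normality of data, statistical tests will be determined". Between arms, numerical data get a t test or Mann-Whitney U, and categorical data get chi-square. No test is assigned to the primary outcome. The threshold is p<0.05 here and again under Statistical Methods.

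**The concern.** A primary outcome needs a variable, a scale, a time and a comparison. Here the comparison is left to the data and the other three are open. The sample size implies a yes/no result per patient, while the outcome section describes a change that could be scored, graded or dichotomised in several ways. Each choice leads to a different test and possibly a different answer. The trial is single blind, so not everyone involved need be unaware of allocation when those choices are made. Two things are at stake. The stated 5% type I error has no defined result to attach to, and the power calculation does not describe the analysis that may be done.

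**Working it through.** **1. The plan's own figure.** Inputs from Target Sample Size: z values 1.96 and 0.84, product term 0.09, difference 0.10.

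n = (1.96 + 0.84)² × 0.09 / 0.10² = 7.84 × 0.09 / 0.01 = 70.56, rounded up to 71.

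The figure reproduces, so the sizing is on a binary outcome. (The section calls 71 a number per group and then enrols 72 in total. That is a separate matter.)

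**2. Does the sizing carry over to a numerical change?** With 36 per arm, 80% power and two-sided 5%, the detectable standardised difference is

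(1.96 + 0.84) × √(2/36) = 2.80 × 0.2357 = 0.66.

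Power for a standardised difference of 0.5 is 56%. Neither figure follows from a difference of 0.10 in proportions, so the sample size section does not support the t or Mann-Whitney route.

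**3. Two candidate days.** Suppose D14 and D28 are each tested at two-sided 5% and either could be taken as the result. The false-positive rate is 1 − P(|Z₁| ≤ 1.96 and |Z₂| ≤ 1.96). For independent tests this is 1 − 0.95² = 0.0975. For correlated tests, from the bivariate normal distribution:

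| Assumed correlation | False-positive rate |
|---|---|
| 0 | 9.75% |
| 0.5 | 9.1% |
| 0.7 | 8.3% |
| 0.9 | 7.0% |

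The protocol gives no correlation, so these are assumptions shown as a range.

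**4. Which tests compete between arms?** The Statistical analysis section puts the paired t test, repeated-measures ANOVA, Wilcoxon signed rank and Friedman under comparisons within a group, and McNemar under responses across time intervals. That leaves chi-square for categorical data and t or Mann-Whitney for numerical data. The normality check decides only between the last two.

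**5. Gain from stratifying a binary outcome by stage.** Assume equal numbers in Stage 1 and Stage 2.
- Success 0.9 and 0.7: within-stage variance (0.09 + 0.21)/2 = 0.15, against 0.8 × 0.2 = 0.16 overall. The ratio is 0.16/0.15 = 1.07.
- Success 0.9 and 0.5: (0.09 + 0.25)/2 = 0.17, against 0.7 × 0.3 = 0.21. The ratio is 1.24.

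The gain is modest.

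**The case against.** The best defence is that test details, covariates and multiplicity are commonly left to a statistical analysis plan, which is not shown. This stands for covariates: an unadjusted comparison of randomised arms is valid, and its absence from the protocol is no fault. It does not cover the outcome itself. The variable, its scale and its time belong in the protocol, and without them the sample size refers to nothing. Choosing the test after a normality check is also a rule that the protocol states, not something it omits.

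Three stronger readings are tempting and are not supported:

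- A reader might infer that all the listed tests compete for the primary result. Most of them are listed for comparisons within a group or across time.
- A reader might infer that endoscopy and biopsy supply further primary readings and push the error rate well above 10%. The only item under the primary outcome is contrast MRI, and the investigations table makes endoscopy with biopsy conditional on need. The synopsis schedules it alongside MRI, which is a conflict over timing and does not make it a co-primary outcome.
- A reader might infer that ignoring baseline stage wastes a large share of the patients. Large gains belong to baseline adjustment of a numerical score. For a binary outcome the gain is small, as shown above.

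It is also fair to say that the protocol nowhere states that either day may be declared the result. It leaves the day open, so the 8% to 10% is conditional.

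**Conclusion.** The concern holds in this limited form. The primary outcome has no scale, event, threshold or deciding day, and the sample size assumes a proportion with an unnamed event. This is a mismatch within the protocol that should be corrected before any comparative data are seen.

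The false-positive rate is about 8% to 10% if either MRI day could count, assuming a correlation of 0.7 down to 0. If one day is fixed in advance, that inflation disappears. No figure is attached to the choice between t and Mann-Whitney, because nothing in the protocol allows one to be calculated.

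Naming the outcome does not repair the power. For illustration, since the protocol does not state the two proportions, 36 per arm has 22% power for 0.90 against 0.80, 29% for 0.95 against 0.85 and 13% for 0.50 against 0.60.

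**What to change.** Name one binary primary outcome that matches the sizing basis. One example is alive at D28 with a lower Annexure 1 main stage or substage than at D0, or no residual disease, on the D28 contrast MRI. Death or progression to Stage 3/4 counts as failure, which also gives a defined result to patients withdrawn for worsening under section 3.5.

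Compare the arms in all randomised patients with one pre-stated test of the difference in proportions, two-sided 5%. This may be stratified by D0 stage (1 or 2), for example as a Mantel-Haenszel risk difference. Make D14, the graded stage and endoscopy/biopsy secondary, and drop the normality-driven choice of test for the primary outcome.

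Three sets of passages must be reconciled first:

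- Duration of intervention provides telephone follow-up after discharge on days 14 and 28, counted from illness. A call cannot supply an MRI reading, and the investigations table schedules MRI at D14 and D28, "D14 and D28, or before or after as per IMP/ requirement" in its own words.
- Follow-up contrast MRI covers the paranasal sinuses only, and imaging of brain and orbits is listed at inclusion alone. The protocol should say how Stage 3/4 would be established at D28.
- In Annexure 1, two Stage 2 substages are printed as 3c and 3d, so a fall in substage cannot be read from the table as it stands.

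The cost is mostly protocol wording. A binary outcome loses some information compared with a graded one, which is why the graded stage is kept as secondary. Discharged patients would need the D28 scan that is already scheduled.
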